## Abstract

**Background:**

Many adults with intellectual disabilities have poor dietary habits, low physical activity and weight disturbances. This study protocol describes the design and evaluation of a health intervention aiming to improve diet and physical activity in this target group. In Sweden, adults with intellectual disabilities often live in community residences where the staff has insufficient education regarding the special health needs of residents. No published lifestyle interventions have simultaneously targeted both residents and staff.

**Methods/Design:**

The intervention is designed to suit the ordinary work routines of community residences. It is based on social cognitive theory and takes 12-15 months to complete. The intervention includes three components: 1) Ten health education sessions for residents in their homes; 2) the appointment of a health ambassador among the staff in each residence and formation of a network; and 3) a study circle for staff in each residence. The intervention is implemented by consultation with managers, training of health educators, and coaching of health ambassadors. Fidelity is assessed based on the participation of residents and staff in the intervention activities. The study design is a cluster-randomised trial with physical activity as primary outcome objectively assessed by pedometry. Secondary outcomes are dietary quality assessed by digital photography, measured weight, height and waist circumference, and quality of life assessed by a quality of life scale. Intermediate outcomes are changes in work routines in the residences assessed by a questionnaire to managers. Adults with mild to moderate intellectual disabilities living in community residences in Stockholm County are eligible for inclusion. Multilevel analysis is used to evaluate effects on primary and secondary outcomes. The impact of the intervention on work routines in community residences is analysed by ordinal regression analysis. Barriers and facilitators of implementation are identified in an explorative qualitative study through observations and semi-structured interviews.

**Discussion:**

Despite several challenges it is our hope that the results from this intervention will lead to new and improved health promotion programs to the benefit of the target group.

**Trial registration number:**

ISRCTN33749876

## Background

Dietary habits, physical activity and obesity are strong modifiable risk factors for chronic diseases such as cardiovascular diseases, diabetes and some cancers [1]. People with intellectual disabilities (ID) often have poor dietary habits [2,3], low physical activity [4,5], and weight disturbances [4-8]. According to a report from the Swedish National Institute of Public Health people with ID carry a higher disease burden than the population in general and interventions directed at these risk factors could be an important way to improve health in this group [9].

In Sweden, individuals with ID who live in community residences are entitled to assistance in everyday life, but the staff often has insufficient education regarding the special needs of people with disabilities [10]. An ID involves a reduced short term memory and a reduced ability for abstraction which increases the risk of making unhealthy choices in an obesogenic environment [11]. IDs are usually categorised as mild, moderate, severe or profound [12]. The categories are arbitrary divisions of a complex continuum, and cannot be defined with absolute precision.

Few lifestyle interventions targeting people with ID have been published. Health programmes, including education, exercise, and in a few cases also stress reduction, have shown modest decreases in BMI [13-17]. In two of those studies, significant improvements were seen in the quality of life in the intervention group after completing the programme [13,16]. In another intervention, where staff received training in meal preparation and weekly supervisor feedback, routines improved and were maintained for up to one year [18]. Positive health changes, in terms of weight loss and decreased blood pressure, were seen in the residents. To our knowledge no interventions have been published targeting both staff and residents in the same community residence. In order to promote sustainability of the intervention it is designed to suit into the normal work routines of community residences. The aim of this paper is to describe and explain the design and evaluation of this health intervention targeting people with ID. The description of the study protocol follows the checklist of the CONSORT statement for cluster-randomized trials [19].

## Methods and design

### Study objectives

1) To study effects of a health intervention on residents' diet quality, physical activity, body mass index (BMI) and quality of life.

2) To study improvements at residence level in work routines and opportunities for healthy diets and physical activity.

3) To describe and analyse barriers and facilitators in the implementation of the intervention.

### Hypothesis

We hypothesise that an educational approach directed both at the residents and staff will strengthen the knowledge and skills of the residents to improve their diet and increase physical activity, as well as the ability of staff to provide a supportive social and physical environment for making healthy choices.

### Setting and target group

Adult men and women with mild to moderate ID who live in community residences in Stockholm County are eligible for inclusion. There are approximately 500 such residences. For a residence to be included, at least three subjects in each residence have to agree to participate. All participants need to have the ability to understand simple information about the study and to decide whether they want to participate or not. A letter of invitation is sent to managers, who are asked to contact their subordinated community residences in Stockholm County. After notification of interest from residences, residents receive an easy-to-read letter with information about the purpose of the study and about the intervention itself. Participants who express interest to participate are informed verbally and in writing, and written consent is obtained. Staff at the residences as well as trustees or legal guardians also receive written and verbal information about the intervention and the purpose of the study. All participants are rewarded with a cinema ticket. Quantitative data will be presented in aggregated form. Qualitative data will be abstracted into themes and illustrated by quotations from the interviews and observations. The data will be treated as strictly confidential and it will not be possible to identify individuals or residences. Ethical permission for this study has been obtained from the Regional Ethical Review Board in Stockholm County No. 2009/1332-31/5.

### Planning of the intervention and development of materials

When planning this intervention we employed the step-by-step approach as described by Fraser et al. [20]. In step 1 we have specified the problem and defined our problem theory. Based on previous research and practitioner's experience, we have identified poor dietary habits, low physical activity and weight disturbances among adults with ID. In addition, the low educational level of staff working in community residences in general has been identified as a barrier to healthy lifestyles among the target group. Our goal with the intervention is therefore to improve diet and physical activity of the residents as well as knowledge and skills of both residents and the staff. The intervention is based on social cognitive theory (SCT). This theory explains behaviour in terms of a triadic, dynamic, and reciprocal model in which behaviour, personal factors, and environmental influences all interact [21]. According to this theory, we aim to improve health behaviours through both personal factors (knowledge, skills, preferences, self-efficacy) of residents as well as through improvements in their social and physical environment, which is very much dependent on knowledge, skills and work routines of the staff.

In step 2 of intervention planning, core components of the intervention are identified and programme materials are developed and pretested. "Fokus hälsa" (Focus health) is a newly developed material with ten themes for use by staff. It aims to increase the knowledge and skills of residence staff with regard to diet, physical activity and health and is based on the principles of peer education [22]. The themes were developed in discussions with managers of community residences and on the basis of their knowledge of the needs of the target group. The themes are: 1) Health and quality of life; 2) Autonomy and ethics; 3) National recommendations concerning diet and health and information in society; 4) Healthy dietary habits; 5) Physical activity for health; 6) Availability and accessibility; 7) Habits and attitudes; 8) Motivation and support for behavioral change; 9) Cooperation; and 10) How to sustain good work. Each theme includes an introductory text, which is read before the meeting, and at the end there are three suggested exercises: 1) Questions for discussion; 2) Identification of strengths and weaknesses in work routines; and 3) Making agreements about new and improved work routines.

A health education material "Hälsokörkortet" (Driver's licence for health) has been developed specifically for people with ID and pretested and revised by "Studieförbundet Vuxenskolan", a national educational association for adults. The material includes ten educational sessions within five areas: diet, physical activity, culture/aesthetics, mental health and stress relief.

### Intervention components

The intervention takes 12-15 months to complete and includes three main components: 1) Ten health education sessions for residents; 2) the appointment of a health ambassador among the staff in each residence, including four network meetings; and 3) a study circle for staff based on the principles of peer education.

#### Health education for residents

The aim of the health education is to support residents to make lifestyle changes in an easy and positive way in their everyday life, by increasing their knowledge, preferences, skills and self-efficacy. Participants get the possibility to try new foods and activities, and are assigned home work. Ten sessions are carried out in the residences by a health educator from "Studieförbundet Vuxenskolan" using the educational material "Hälsokörkortet" (Driver's licence for health). The material includes themes and detailed instructions for the educator for each of the ten sessions. Each session is supposed to last for 2 × 45 minutes and comprises of a discussion, a theme activity, testing of healthy food, physical activity and homework.

#### Health ambassadors

Ambassadors for various issues are common among the staff in community residences and we wanted to build on this practice. Therefore, in every participating community residence a health ambassador is appointed among staff members. The task of the health ambassador is to provide health information to colleagues and inspire them and to plan and organise health promoting activities for residents. The health ambassador receives coaching by the research team on issues regarding diet, physical activity and health and gets the possibility to exchange knowledge and experiences during network meetings with health ambassadors from the other residences. Network meetings are arranged four times during the intervention. The first meeting is an introductory meeting and following meetings focus on themes chosen by the ambassadors.

#### Study circle for staff

The aim of the study circle is to increase the knowledge and skills of staff in the area of health promotion in order to empower them to improve work routines and the social and physical environment of residents. Normally, staff in community residences meet once every second or fourth week. We decided that these meetings would be a good opportunity for the staff to conduct this study circle using the study material "Fokus Hälsa" (Focus Health). All the staff in every community residence, including the health ambassador, comes together to discuss health issues, based on the principles of peer education [22]. A discussion leader is appointed and the group discusses and does the exercises according to the instructions in the material.

### Implementation components

Implementation components or drivers are factors which enable practitioners to implement the intervention as intended [23]. Typical components used in this programme are consultations with managers, training and coaching of staff. First, managers and staff in the residences are invited to an introductory meeting discussing the entire intervention with the research team. Second, the health educators are trained by the research staff together with experienced educators from "Studieförbundet Vuxenskolan" for one day regarding how to use the material "Hälsokörkortet" (Drivers licence for health). During the entire intervention period the health ambassadors receive coaching on demand from the research group via personal visits, mail, telephone, and at network meetings. Newsletters are sent to all residences to keep staff and residents up to date with the overall state of the project and important news. Figure 1 shows the logic model of the intervention explaining the hypothetical causal chain that may lead to behaviour changes of the target group.

**Figure 1 F1:**
[figure not shown]
**Logic model of the intervention in community residences**.

### Evaluation design

Step 3 in intervention research [20] constitutes the evaluation of the intervention with regard to individual outcomes and setting level impacts. Because we are targeting both residents and staff the study is designed as a cluster-randomised trial. After baseline measurements are completed, residences are randomised to an intervention group and to a waiting list-control group by a computer-generated list of random numbers done by the statistician, and concealed from the research staff, which enrols the participants. Evaluation is done by mixed methods, using both quantitative and qualitative methods.

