#### Statistical power

Calculation of power is based on the assumption of an average 25% increase in physical activity, assessed as steps per day by pedometry. No Swedish data were available so we used data from Peterson et al [31] from the USA for adults with mild to moderate intellectual disabilities, who on average achieved 6621 ± 3366 steps per day. Calculations were performed with the "Sample size calculator for cluster randomized trials" [32]. The calculation was 2-sided, and power was set to 80%, the significance level to 5%, and cluster size to five individuals. The calculation shows that 32 community residences are needed to detect a significant change in physical activity of 25% between the intervention and control group.

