#### Data analysis

Data analysis will be performed by the statistician who is blinded to the intervention group assignment. At individual level, parametric and non-parametric tests are used to compare groups at baseline, depending on the distributions of the quantitative variables. In order to account for clustering of the data, multilevel analysis is used to evaluate the effects of the intervention on relevant outcomes. Two levels are defined in the analysis: 1) individual and 2) residence. Linear and logistic regression models are used to study the effect on the outcome variables physical activity, intake occasions of indicator foods, meal quality, dietary diversity, body weight status, BMI and quality of life. Intervention outcome will be evaluated in relation to the intervention dose (fidelity score) but also to the intention to treat principle.

To evaluate the impact of the intervention on work routines and opportunities for a healthy diet and physical activity in community residences ordinal regression will be used for the data derived from the questionnaire Work routines for meals, physical activity and health (Additional file 1). Multinomial logistic regression might also be used if it is the categories and not the order of the categories per se that is of importance for the results. If the dependent variable can be adequately dichotomised, we will use Poisson regression with robust error variance (modified Poisson regression) to estimate risk ratios (relative risks).

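### About 32 residences are allocated with no stated balancing on baseline steps, although steps are measured first; the cost is avoidable chance imbalance, not bias or a shortfall in planned power

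*Protocol article*

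**What the plan says.** The section Evaluation design gives the order of events, "After baseline measurements are completed, residences are randomised", and the method: "residences are randomised to an intervention group and to a waiting list-control group by a computer-generated list of random numbers". The statistician makes the list, and it is kept from the staff who enrol participants. Neither this section nor any other names an allocation ratio or any form of restricted randomisation.

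The section Intervention outcomes has every individual-level outcome measured at baseline. That includes the primary outcome, average steps per day.

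The section Statistical power concludes that "32 community residences are needed to detect a significant change in physical activity of 25% between the intervention and control group". Its settings are: "The calculation was 2-sided, and power was set to 80%, the significance level to 5%, and cluster size to five individuals". No ICC is given.

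The section Data analysis says that "parametric and non-parametric tests are used to compare groups at baseline". It then plans a two-level model (individual, residence) for the effect of the intervention, and names no adjustment for baseline steps.

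**The concern.** Thirty-two clusters is a small number to balance by chance alone, and the primary outcome varies widely: the assumed SD is 3366 steps against a target difference of 1655. A sizeable baseline gap between arms is therefore quite likely. It would make the result harder to interpret, whether the trial looks positive or negative.

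The variable that matters most for balance, baseline steps, is known for each residence before it is allocated. Using it in the allocation would narrow the gap in advance. Testing for baseline differences afterwards does not: the test neither prevents nor corrects a chance imbalance, and under proper randomisation it tests a hypothesis already known to be true. The allocation also cannot be revised once it is made, whereas a covariate can still be added to the model.

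**Working it through.** **Inputs.** From Statistical power: mean 6621, SD 3366, increase 25%, two-sided 5%, power 80%, five per residence, 32 residences. Assumptions: ICC 0.05 (range 0 to 0.20), equal residence sizes, 1:1 allocation, normal approximation.

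**1. The plan's own figure.** The target is 0.25 × 6621 = 1655.25 steps. Without clustering, n per arm = 2 × [3366 × (1.960 + 0.842) / 1655.25]² = 64.9. The design effect at ICC 0.05 is 1 + 4 × 0.05 = 1.2. Residences per arm = 64.9 × 1.2 / 5 = 15.6, rounded up to 16, so 32 in total. The stated figure is reproduced. With this formula exactly 16 per arm follows for an ICC from about 0.039 to 0.058; ICC 0 gives 26 residences in total and ICC 0.10 gives 38.

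**2. Chance gap in baseline steps at exactly 16:16, no restriction.** SD of the difference in arm means = 3366 × √[(1 + 4 × ICC)/5 × 2/16].

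| ICC (assumed) | SD of gap (steps) | Share of 1655 | P(gap > 828, half the target) |
|---|---|---|---|
| 0 | 532 | 32% | 12% |
| 0.05 | 583 | 35% | 15.6% |
| 0.10 | 630 | 38% | 19% |
| 0.20 | 714 | 43% | 25% |

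At ICC 0.05: 3366 × √0.03 = 583; 827.6/583 = 1.42, two-sided probability 0.156; the 95% range is 1.96 × 583 = ±1143 steps.

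**3. Is this already in the planned power?** The same 583 is the standard error behind an unadjusted comparison at follow-up, if SD and ICC are unchanged. 1655.25/583 = 2.84; 2.84 − 1.96 = 0.88; power = 81.0%. So yes, at the ICC that reproduces the 32 residences.

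**4. Arm sizes, only if each residence were allocated by an independent coin flip.** From Binomial(32, 0.5), a split of 20:12 or more uneven has probability 21.5%, and 22:10 or more uneven 5.0%. Power is 81.0% at 16:16, 78.5% at 20:12 and 74.9% at 22:10. Averaged over all splits it is 79.7%, a loss of 81.0 − 79.7 = 1.3 points.

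**5. What restriction would gain.** Simulation with 20,000 replicates, ICC 0.05, normally distributed residence means, 16:16, equal-sized strata formed by ranking residence mean baseline steps:

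| Allocation | SD of gap (steps) | P(gap > 828) |
|---|---|---|
| No strata | 580 (formula: 583) | 15.3% (formula: 15.6%) |
| 2 strata | 356 | 2.1% |
| 4 strata | 226 | 0.04% |
| 16 matched pairs | 102 | none seen |

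**The case against.** - **The text does not say the allocation is unrestricted.** A random-number list fits ranking the residences and splitting them 16:16, or drawing within blocks or strata, as well as it fits coin flips. The article may also have condensed a fuller protocol. This stands. A reader might infer that arm sizes are left to chance, but the document does not support that as a fact, and the average cost would be only 1.3 points of power. What remains is that the method is described and no use of baseline steps appears in it.
- **The gap is already paid for.** The 583-step figure is the standard error inside the sample size, and simple randomisation is unbiased. This also stands. A reader might infer that the trial is biased or falls below its planned power; at 16:16 and ICC 0.05 neither is so. Restriction with adjustment improves on the plan and does not repair a deficit.
- **Covariate adjustment could recover much of the precision, and an analysis plan that is not shown may specify it.** This is fair. The figures above describe the raw baseline gap, not its effect on an adjusted estimate. That effect depends on the correlation between baseline and follow-up steps, which the article does not give. Adjustment in the model does not give balance that readers can see, so the two measures complement each other.
- **Balancing is not free.** The article does not say whether residences are randomised together or in waves, and its Discussion says they are not easy to recruit. Waiting for baseline across the whole trial could be a burden. This stands and shapes the fix.

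**Conclusion.** The point holds as a design improvement. As described, the allocation makes no use of baseline steps that are in hand beforehand. Under an assumed ICC of 0.05 this leaves, even at 16:16, a chance baseline gap with an SD of about 583 steps (532 to 714 over ICC 0 to 0.20), or 35% (32 to 43%) of the target. A gap of more than half the target would occur in about one trial in six (12 to 25%). What can be gained is precision and ease of interpretation above the plan.

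The figures rest on the unstated ICC, five participants in every residence and the SD taken from the earlier US study. If the true ICC were well above 0.058, 32 residences would fall short of 80% power however they were allocated; that is a separate matter.

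**What to change.** 1. State the allocation ratio and any restriction. Allocate 1:1 within strata of residence mean baseline steps and number of participants, or by constrained randomisation on both. With 32 residences, two to four step strata already achieve most of the reduction; constraint is the simpler route if crossing two factors would leave very small strata.
2. If residences are randomised in waves, apply this within each wave. The simulated gains assume that all 32 are ranked together and would differ with small waves.
3. Include the balancing factors and each participant's baseline steps in the two-level model.
4. Replace the baseline tests with a descriptive table by arm.

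The cost is a few lines of code for the statistician who already makes the list. Allocation must wait until baseline is complete for the residences or wave concerned, an order the plan already sets with "After baseline measurements are completed", and the balancing factors must be carried into the analysis.
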